### Outcome assessment

The primary outcome measures that will be considered to assess the effectiveness of the intervention are the symptoms presented by the patients and the degree of overload experienced by the caregivers. The secondary outcomes considered, for patients and caregivers, are health-related quality of life, satisfaction with the intervention and the economic valuation. The outcome measures will be obtained from questionnaires completed at the start of the study (t0), at 1 week after randomisation (t1) and at 1 month after the start (t2).

### Primary outcome measure. Variables and measurement instruments for patients

Patients’ symptoms will be evaluated by the Edmonton Symptom Assessment System (ESAS), validated in Spanish [43]. This instrument considers ten frequently-occurring symptoms in cancer patients – pain, tiredness, nausea, depression, anxiety, drowsiness, dyspnoea, anorexia, sleep disorders and malaise – that may have been experienced by the patient during the previous week. The patient is asked to select the number that best indicates the intensity of each symptom, on a scale ranging from zero to ten (0 = no symptom, 10 = maximum severity). The ESAS symptoms are then classified as the physical component (pain, shortness of breath, lack of appetite, nausea, tiredness and drowsiness) and the psychological component (anxiety and depression), which are combined to produce the overall ESAS score.

### Secondary outcome measures. Variables and measurement instruments for patients

Sociodemographic data for patients in palliative care: age, sex, marital status, level of education, type of cancer and time spent in palliative care.Health-related quality of life will be assessed according to the 30-item core European Organisation for Research and Treatment of Cancer Quality of Life Questionnaire (EORTC QLQ C30), version 3.0, validated in Spanish [44]. In this instrument, items 1–28 are based on mixed categorical scales ranging from 1 to 4 and refer to the patient’s functional status, the presence of physical and emotional symptoms and their impact on work and socio-family life. Items 29 and 30 assess general aspects of the patient’s health and quality of life, on a scale ranging from 0 to 7. This scale is used to assess the quality of life of patients in palliative care.Quality-Adjusted Life Year (QALY). This parameter is obtained according to the European Quality of Life-5 Dimensions-5 Levels (EuroQol-5D-5 L) questionnaire [45], validated in Spanish [46], which describes the patient’s health status in five dimensions (mobility, personal care, usual activities, pain/discomfort and anxiety/depression). Results are also obtained on a visual analogue scale (VAS), graduated from 0 to 100, representing the range from “worst imaginable health status” to “best imaginable health status”, respectively.Use made of health resources: number of consultations in primary care (family doctor and family nurse), number of home visits (family doctor, family nurse and case manager), number of consultations made to the primary care emergency service, number of consultations made to the hospital emergency department and number of hospital admissions (recording the number of days of admission). The time spent by health care personnel in responding to telephone calls to the palliative care unit and to the case manager will also be taken into account.Consumption of medication - analgesics, anxiolytics and sleeping pills.Willingness to pay. The patients’ willingness and ability to pay for musical therapy will be evaluated using the contingent valuation method [47] in which, in a hypothetical scenario, patients are asked whether they would be prepared to pay for music therapy.Satisfaction with palliative care. The patient’s satisfaction with the care received will be determined using the CSQ-8 Client Satisfaction Questionnaire, a self-administered instrument consisting of 8 questions, evaluated on a 4-point Likert scale, with specific cut-off points for each item. The questionnaire focuses on the quality and type of service received, the results achieved and overall satisfaction. Also included are three open questions, inviting the respondent to describe the best and worst aspects of the service received, and the changes that should be made. This instrument determines patient satisfaction with high reliability and consistency, and has been validated, in its 8-item version, for use with a Spanish-speaking population [48]. This version, too, provides high internal consistency and concurrent validity.

### Primary outcome measure. Variables and measurement instruments for caregivers

Caregiver overload is assessed by the Caregiver Strain Index (CSI) [49], using a questionnaire translated and adapted for a Spanish-speaking population [50]. The CSI is designed for caregivers of dependent people in general, not specifically those receiving palliative care. The format used is that of a semi-structured interview, consisting of 13 true-false items. Each affirmative answer is scored as 1 point and a total score of 7 or more points is indicative of a high level of strain.

### Secondary outcome measures. Variables and measurement instruments for caregivers

Sociodemographic data for caregivers: age, sex, marital status, level of education, working outside home (yes/no), time spent providing daily care, help received in providing care, total time spent providing care, and relationship with the person receiving care.The quality of life of the caregiver will be assessed by the Family Quality of Life (FQOL) scale [51], which measures the quality of life of a family member caring for a patient with cancer. The possible scores on this scale range from 0 = worse result to 10 = best result, and the total score possible ranges from 0 to 100. Some of the items are awarded an inverse score, and so when the results are tallied and coded, the scores for those elements must be reversed. The FQOL, which has been validated for use with a Spanish-speaking population [52], addresses physical, psychological, spiritual and social aspects of the caregiver’s experience.QALY.Use made of health resources: similar to the assessment made in this respect of the patient receiving palliative care.Consumption of medication: similar to the assessment made in this respect of the patient receiving palliative care.Willingness to pay: similar to the assessment made in this respect of the patient receiving palliative care.Satisfaction, CSQ-8.

An overview of the primary and secondary outcome measures is shown in Table 1.

**Table 1 Tab1:** Measurement overview

Patient		T0	T1 7 days	T2 30 days
Primary outcome	Edmonton Symptom Assessment System (ESAS)	X	X	
Secondary outcomes	The Quality of Life of Cancer Patients (EORTC. QLQ-30)	X	X	
	Quality-Adjusted Life Year (QALY)	X	X	
	EuroQol-5D-5 L	X	X	
	Variables cost-utility analysis			
	Health Resources Consumption	X	X	X
	Medication consumption (analgesics, anxiolytics, sleeping pills)	X	X	X
	Availability to pay		X	
	Client Satisfaction Questionnaire (CSQ-8)		X	
	Other variables			
	Sociodemographic data: age, sex, marital status and level of education.	X		
	Palliative care time	X		
	Type of cancer	X		
**Caregiver**		**T0**	**T1 7 days**	**T2 30 days**
Primary outcome	Caregiver Strain Index (CSI),	X	X	
Secondary outcomes	The Quality of Life Family Version (QOL)	X	X	
	Quality-Adjusted Life Year (QALY)	X	X	
	EuroQol-5D-5 L	X	X	
	Variables cost-utility analysis			
	Health Resources Consumption	X	X	X
	Medication consumption (analgesics, anxiolytics, sleeping pills)	X	X	X
	Availability to pay		X	
	Client Satisfaction Questionnaire (CSQ-8)		X	
	Other variables			
	Sociodemographic data: age, sex, if you work away from home, marital status and level of education.	X		
	Time spent on care	X		
	Care support	X		
	Caring time	X		
	Relationship with the caregiver	X		

### Statistical analysis

A descriptive study will be made of the variables collected, calculating the mean and standard deviation in each case for the normally-distributed continuous variables, the confidence interval as appropriate for specific estimates, the median and interquartile range for non-normally-distributed continuous variables, and frequencies and percentages for categorical variables. The normality of the distribution will be determined by the Shapiro-Wilk test. Baseline values for the two groups will be compared.

The before and after-intervention values, in the control and intervention groups, will be compared by Student’s t-test for related samples in the case of normal continuous variables, and by the Wilcoxon T-test for paired data in the case of non-normal continuous variables.

In addition to this bivariate analysis, a multiple linear regression will be performed, in which the following dependent variables will be addressed, depending on the case: pain, fatigue, nausea, depression, anxiety, drowsiness, dyspnoea, anorexia, sleep disorders, malaise/well-being and quality of life. The independent variables considered will include both the intervention itself and also the participants’ sociodemographic variables (sex, age, level of education, marital status) and clinical variables (pathology, total time receiving palliative care). A similar procedure will be followed to determine the significance of the consumption of analgesics and the number of visits made by the nurse. All results obtained will be presented at a confidence interval of 95%. Thus, *p* < 0.05 is assumed to be statistically significant. The statistical software SPSS 23 and Epidat 4.2 will be used in this analysis.

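### A Shapiro-Wilk pre-test chooses the summaries and within-arm before-after tests, and for the CSI and overall ESAS score such a test is the only analysis of change named

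*Protocol article*

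**What the plan says.** All of this is in the Statistical analysis section of the protocol article unless noted.

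- **The deciding rule:** "The normality of the distribution will be determined by the Shapiro-Wilk test". No significance level is given for it. The section does not say whether it is applied per arm or pooled, or to raw scores or changes.
- **Summaries:** mean and SD for variables judged normal; "the median and interquartile range for non-normally-distributed continuous variables".
- **Before-after tests:** "The before and after-intervention values, in the control and intervention groups, will be compared", and the method follows the verdict. Values "will be compared by Student’s t-test for related samples in the case of normal continuous variables", and otherwise "by the Wilcoxon T-test for paired data in the case of non-normal continuous variables". Both are paired tests, so each works inside one arm.
- **A second analysis:** "In addition to this bivariate analysis, a multiple linear regression will be performed". The listed dependent variables are the ten ESAS symptoms and quality of life, with a similar procedure for analgesic use and nurse visits. The intervention is an independent variable, alongside sociodemographic and clinical characteristics. The baseline score is not listed.
- **Significance:** p "< 0.05 is assumed to be statistically significant".

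The outcome sections make the ESAS the patients' primary measure, with each item scored "on a scale ranging from zero to ten (0 = no symptom, 10 = maximum severity" and an overall score formed from the components. They make the CSI, a count over 13 true-false items, the caregivers' primary measure. Table 1 places both at T0 and T1.

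**The concern.** Bounded integer scores in arms of 33 to 41 people sit where a normality test gives unstable verdicts: two arms drawn from the same distribution can fall on opposite sides by chance. If the verdict is taken arm by arm, one arm could be reported as a mean change with a t-test and the other as a median with a Wilcoxon test. Those two results cannot be subtracted to give a treatment effect.

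The choice matters most where nothing else is planned. The regression list omits the CSI and the overall ESAS score. For these the pre-tested paired comparison is the only test of change the section names. Whichever branch it takes, it asks whether an arm changed over time, not whether the arms differ.

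**Working it through.** **1. The plan's own figure.** Inputs from the Sample size section: difference 2, SD 2.5, alpha 0.05, power 0.90, ratio 1:1.

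n per group = 2 × (1.960 + 1.282)² × 2.5² / 2² = 2 × 10.51 × 1.5625 = 32.8, so 33, as stated. 33 × 1.2 = 39.6, so 40, as stated. The figure is reproduced by the two-sided, two-sample formula, so the trial is already sized for a between-arm comparison.

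**2. How often the arms would receive different tests.** The documents give no baseline mean, no before-after correlation and no level for Shapiro-Wilk, so these are assumptions. T0 and T1 scores were simulated as bivariate normal with SD 2.5 and correlation 0.5, rounded and cut to 0-10. The distribution was the same in both arms with no treatment effect, Shapiro-Wilk was applied at 0.05, and there were 2,000 trials per setting. At correlation 0.5 the SD of a change is 2.5 × √(2 × (1 − 0.5)) = 2.5 before rounding, so the input suits either reading of the protocol's SD.

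Normality judged per arm on change scores:

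| Latent mean | n per arm | P(judged normal) | Arms differ, simulated | 2p(1 − p) |
|---|---|---|---|---|
| 5 | 33 | 0.853 | 25.6% | 25.1% |
| 4 | 33 | 0.853 | 24.7% | 25.1% |
| 3 | 33 | 0.830 | 28.8% | 28.2% |
| 2 | 33 | 0.723 | 39.6% | 40.1% |
| 5 | 40 | 0.841 | 25.7% | 26.7% |
| 4 | 40 | 0.830 | 29.0% | 28.2% |
| 3 | 40 | 0.795 | 34.0% | 32.6% |
| 2 | 40 | 0.676 | 41.1% | 43.8% |

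The last column is the value expected for two independent arms that each pass with probability p; it agrees with the simulation to within about 3 points. The range is about 25-41%.

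Other readings and settings:
- Exactly normal continuous data, change scores: 9-12%.
- Latent means of 1 and 0 with 40 per arm: 45% and 8%.
- Judged per arm on raw baseline scores: about 1-49%, depending on the mean.
- Judged once per variable: 0% by construction.

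**3. Effect on error rates.** In the same settings, within-arm type I error was:
- always paired t: 4.5-5.7%
- always Wilcoxon: 4.4-5.7%
- Shapiro-Wilk first, then the indicated test: 4.7-5.7%

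The t-test and the Wilcoxon test reached different decisions at 0.05 in about 1-2% of datasets.

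**4. What each outcome is left with.**

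| Outcome | Pre-tested within-arm test | Regression with intervention term |
|---|---|---|
| Ten ESAS items | yes | yes, baseline score not listed |
| Quality of life | yes | yes, baseline score not listed |
| Overall ESAS score | yes | not listed |
| CSI | yes | not listed |

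**5. What baseline adjustment adds.** With correlation 0.5, the residual variance of the T1 score given T0 is (1 − 0.5²) = 0.75 of the unadjusted variance. The unadjusted change score has 2 × (1 − 0.5) = 1.00 of it. The standard error of the arm difference therefore falls to about √0.75 = 0.87 of its unadjusted value, whichever of the two is the dependent variable.

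**The case against.** The strongest reply is that little inferential harm is shown, and most of it stands.

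- **A reader might infer that the two arms will be handled differently.** The document does not say so. It speaks of normal and non-normal variables, which fits one verdict per variable. Per-arm testing is a natural companion to within-arm tests and is not ruled out, but it remains one permitted reading. Such details may also sit in a fuller plan. The percentages are conditional on that reading.
- **A reader might infer that no common effect estimate exists for the primary outcome.** For the ten ESAS items this is wrong: the regression does not depend on Shapiro-Wilk and gives one between-arm coefficient per symptom. The statement holds only for the CSI and the overall ESAS score, and there the cause is the missing between-arm comparison. Using a t-test in both arms would not supply it.
- **A reader might infer inflated false positives.** The error rates in the working show none.
- **A reader might infer that the analysis is chosen freely after the data are seen.** The rule and both branches are written in advance; the data settle only which branch a variable takes.

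It is also fair to say that the weightier weakness in this section is the reliance on within-arm tests, and that curing it makes the pre-test irrelevant. That is why the fix deals with both. The reply does not remove two facts: the pre-test brings no gain in validity in these settings, and the caregivers' primary outcome is left with no named between-arm analysis.

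**Conclusion.** The point holds in a limited form and is of low severity. Shapiro-Wilk decides the summaries and the within-arm before-after tests, not the regression. If it is applied per arm to change scores, the arms of one 0-10 item would be tested differently in about 25-41% of trials, assuming correlation 0.5, level 0.05 and latent mean 2 to 5; if applied once per variable, never. Error rates stay near 5% either way. The substantive gap is confined to the CSI and the overall ESAS score, for which the only named test of change is a within-arm one that gives no between-arm effect. For the ESAS items and quality of life a between-arm estimate exists, but its listed covariates leave out the baseline score and so forgo precision. The documents give no correlation or baseline mean, so the percentages and the precision gain are illustrative.

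**What to change.** Remove the Shapiro-Wilk test as the rule for choosing methods. For the ESAS items, the overall ESAS score and the CSI, state one primary method in advance: the between-arm mean difference at T1, adjusted for the T0 value, with a robust or bootstrap 95% interval. Show mean (SD) and median (IQR) for both arms, whatever the shape of the distribution. Keep a rank-based test as a named sensitivity analysis.

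The cost is a small rewrite of the Statistical analysis section. The T0 and T1 values are already collected under Table 1, so no new data are needed, and the sample size stays at 33 per group before losses for patients and 34 for caregivers.

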### Sample size

The most significant variable in palliative care patients is assumed to be anxiety. In a review conducted by Bradt et al. [29], this variable presented a distribution with a standard deviation of 1.8, for a population similar to that considered in the study we propose, albeit with a wider range of results. Previous studies have reported that music therapy has a significant impact on this variable. In one case, an effect size of 7 was measured (effect size of 29% of the standard deviation). Another study, of cancer patients receiving treatment including ginseng [39], recorded a variation of 0.83 points on the Edmonton scale, with a standard deviation of 2.34 (35% of the standard deviation). Assuming a 2-point decrease in before-after anxiety to be clinically relevant, and a maximum standard deviation of 2.5 in our population, with an alpha error of 0.05 and a beta of 0.10, we calculate that two samples of 33 subjects will be necessary, to enable the option of a 1:1 ratio between the samples. For convenience, and to allow for losses to follow up, this sample size will be increased by 20%, to two samples of 40 persons. The Epidat 4.2 statistical program was used to perform these calculations.

Hanser et al. [40] recorded an increase in caregivers’ satisfaction following the incorporation of music therapy into the healthcare provided, with a standard deviation of 1.33 for relaxation, 1.87 for comfort, and 1.23 for happiness. Taking into account these findings and assuming an increase of one point in the dimension of caregiver happiness to be clinically relevant, we calculate that two samples of 34 caregivers will be necessary. For convenience, this sample size will be increased by 20%, to two samples of 41 persons, to allow for losses to follow up.

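### The stated before-after tests are within-arm and cannot compare the randomised groups; the CSI has no stated between-arm test, and the ESAS is compared between arms only symptom by symptom

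*Protocol article*

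**What the plan says.** All statements are in the Protocol article.

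- **Primary outcomes.** Outcome assessment names patients' symptoms and caregivers' overload. The instrument sections and Table 1 measure these by the ESAS and the CSI at T0 and T1. The ESAS section also defines an overall score but does not expressly name it as the primary endpoint.
- **Bivariate tests.** Statistical analysis says "The before and after-intervention values, in the control and intervention groups, will be compared by Student’s t-test for related samples" for normal variables and "by the Wilcoxon T-test for paired data in the case of non-normal continuous variables". The only two-group comparison named in this part is at baseline: "Baseline values for the two groups will be compared".
- **Regression.** A multiple linear regression is added. Its outcomes are "pain, fatigue, nausea, depression, anxiety, drowsiness, dyspnoea, anorexia, sleep disorders, malaise/well-being and quality of life". On the predictors, "The independent variables considered will include both the intervention itself and also the participants’ sociodemographic variables", followed by clinical variables. The T0 score is not among those listed. The same approach is extended to analgesic consumption and nurse visits. Neither the CSI nor the overall ESAS score is mentioned.
- **Sample size.** For patients, "we calculate that two samples of 33 subjects will be necessary, to enable the option of a 1:1 ratio between the samples".

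**The concern.** The aim is comparative: music against usual treatment. A before-after test in one arm mixes any effect of music with natural course, regression to the mean, attention and reporting effects. Both arms receive usual care plus seven daily audio sessions, so some shared change is plausible. If the two arms are then judged by whether each reaches significance on its own, the type I error of the arm comparison is not controlled, and a real difference can be hidden when both arms improve.

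What is at stake differs by sample. For caregivers, the primary question would be answered without any stated use of the randomisation. For patients, the arms are compared on each symptom, but not on the summary score that the protocol itself defines.

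**Working it through.** **1. Which outcome meets which test**

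| Outcome | Paired within-arm test | Model with treatment |
|---|---|---|
| Ten single ESAS symptoms | yes | yes |
| Overall ESAS score | yes | not listed |
| CSI (caregivers' primary) | yes | not listed |
| Quality of life | yes | yes |

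The first column assumes that the general statement about paired tests covers every continuous outcome.

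**2. What the sample size was computed for**

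Inputs from the Sample size section: difference 2, SD 2.5, alpha 0.05 (taken as two-sided), power 0.90. (1.960 + 1.282)² = 10.51.

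- Two independent samples: n = 2 × SD² × 10.51 / difference² = 2 × 6.25 × 10.51 / 4 = 32.8, so **33 per arm, as stated** (34 by the noncentral t).
- One paired sample, same inputs: n = 6.25 × 10.51 / 4 = 16.4, so **17** (19 by the noncentral t). This does not give 33.
- Caregivers, 1 point on happiness, SD 1.23, power taken as 0.90: 2 × 1.5129 × 10.51 = 31.8, so 32 (33 by the noncentral t), close to the stated 34. The paired version gives 18 by the noncentral t.

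The trial was sized for a between-arm comparison.

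**3. What happens if within-arm significance is used as the comparison**

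Assumptions, not in the protocol: no true arm difference, both arms improve by c points, SD of change 2.5 (the patients' anxiety figure; none is given for the CSI), 33 per arm. Let p be the chance that one arm improves significantly: p = P(T > 2.04), where T is noncentral t with 32 df and noncentrality c√33 / 2.5. The arms are independent, so the chance that music is significant and control is not equals p(1 − p).

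| Common improvement c | p | p(1 − p) |
|---|---|---|
| 0 | 0.025 | 2.4% |
| 0.5 | 0.199 | 15.9% |
| 0.85 | 0.474 | 24.9% |
| 1.0 | 0.606 | 23.9% |
| 1.5 | 0.916 | 7.7% |

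A valid two-sided 5% test gives 2.5% in that direction. A simulation of 50,000 trials at c = 0.85 gave 24.7% for the within-arm rule and 4.9% (both directions) for the two-sample test. Because p(1 − p) cannot exceed 0.25, about 25% is the ceiling whatever the SD.

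**4. The opposite error**

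With a true difference of 2 points, both arms are significant, and the contrast is hidden, in 2.5% of trials if control improves by 0, 60.6% if by 1 and 99.4% if by 2.

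**5. The between-arm test at the planned size**

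For 2 points and SD 2.5, power is 0.901 at 33 per arm (0.893 by the noncentral t) and 0.947 at 40 (0.942).

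**The case against.** The strongest reply is that the regression already compares the arms. Its treatment coefficient is an adjusted between-arm contrast for every ESAS symptom, including anxiety, on which the patient sample size rests. Since the patient primary outcome is stated as symptoms, a reader who concluded that the randomised comparison is not tested at all would be wrong. This stands for patients. It does not help the CSI, which is in neither the outcome list nor its extension.

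Three other stronger readings are tempting and also fail:

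- **The overall ESAS score as a declared primary score.** It is defined, but no section declares it primary.
- **The paired tests as the main analysis.** The text puts them first and the regression second, but ranks neither.
- **A conflict with intention to treat.** Control of bias says nothing on missing T1 values, and handling them may properly sit in an analysis plan. A linear model of T1 on arm and T0 would also lose people without T1 unless missing data were handled.

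It is also fair to say that the protocol nowhere states the rule of significant in one arm and not in the other. The error rates above describe a likely use of the paired tests where no between-arm test exists. They are not the protocol's type I error for the single symptoms. Finally, the predictor list is worded as what will be included, so the T0 score is unlisted rather than ruled out.

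An unseen analysis plan does not settle the matter, because the article is not silent here: it names specific tests and a specific outcome list.

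**Conclusion.** The point holds in this form. The stated bivariate tests are within-arm and cannot compare the randomised groups, although the sample size is that of a two-sample comparison (33 per arm, against 17 to 19 for a paired test). The CSI, one of the two primary outcomes, has no stated between-arm test. The ESAS has one only symptom by symptom, in a model that does not list the T0 score.

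If within-arm significance filled the gap, the chance of a false finding for music would run from 2.4% to 24.9% over common improvements of 0 to 1.5 points, against 2.5%. This range rests on the assumed shared improvement, the assumed change SD of 2.5 and 33 per arm. With no shared change there is no inflation. The gap for the CSI rests on no numerical assumption and needs correcting before analysis.

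**What to change.** In the Statistical analysis section:

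1. For caregivers, state a between-arm difference in the T1 CSI with 95% CI, from a linear model with arm and T0 CSI, with participants analysed as allocated.
2. For patients, state the same for the T1 overall ESAS score, alongside the single symptoms already listed, each with its T0 score in the model.
3. Add the CSI and the overall ESAS score to the list of dependent variables.
4. Keep the paired before-after comparisons as description, and say that they are not the basis for conclusions about efficacy.

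The cost is a change of wording. Table 1 already schedules both instruments at T0 and T1, so no new data are needed. The planned size still serves the 2-point anxiety target. Power for the CSI or the overall ESAS score cannot be computed from the protocol, because it gives no SD or target difference for either.

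### No single test decides the patient primary outcome: the only model containing the intervention tests ten unranked ESAS symptoms at p<0.05 and omits the overall ESAS score

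*Protocol article*

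**What the plan says.** Four parts of the protocol article bear on the patient efficacy claim.

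- **Outcome assessment:** "The primary outcome measures that will be considered to assess the effectiveness of the intervention are the symptoms presented by the patients", alongside caregiver overload. Table 1 lists the ESAS on one line, measured at T0 and T1.
- **Primary outcome measure (patients):** "This instrument considers ten frequently-occurring symptoms in cancer patients", each scored 0 to 10. Six are assigned to a physical and two to a psychological component, "which are combined to produce the overall ESAS score".
- **Sample size:** "The most significant variable in palliative care patients is assumed to be anxiety". The calculation uses a 2-point difference, SD 2.5, alpha 0.05 and beta 0.10, and gives 33 per group, raised to 40. Anxiety is not declared the deciding endpoint.
- **Statistical analysis:** paired before-after tests are described first. A multiple linear regression is then added, with these dependent variables: "pain, fatigue, nausea, depression, anxiety, drowsiness, dyspnoea, anorexia, sleep disorders, malaise/well-being and quality of life". Treatment enters this model as a covariate, next to sociodemographic and clinical factors. For all results, p below "0.05 is assumed to be statistically significant".

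**The concern.** The outcome that is defined (an overall score), the outcome the trial is sized on (anxiety) and the outcomes that are modelled against treatment (ten separate symptoms) differ, and no sentence says which one decides. The paired tests do not fill the gap: they compare before with after and are not tied to the overall score.

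The Discussion foresees use in practice if effectiveness is demonstrated. With ten unranked coefficients each judged at 0.05, a report could rest that conclusion on whichever symptom crosses the threshold. The 5% level would then not describe the error rate of the patient claim.

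This is multiplicity inside one outcome in one population. It is separate from the fact that patients and caregivers each have a primary outcome.

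**Working it through.** **1. The plan's own figure.** Inputs from Sample size: difference 2, SD 2.5, two-sided alpha 0.05, power 0.90, ratio 1:1. The text words the difference as a before-after decrease, but the formula for two independent groups reproduces the number:

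n = 2 × (1.960 + 1.282)² × (2.5/2)² = 2 × 10.51 × 1.5625 = 32.8, so 33 per group. Then 33 × 1.2 = 39.6, so 40.

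The figure of 33 therefore belongs to one test, on anxiety, at 0.05.

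**2. Number of tests.** The regression list has eleven entries. Removing quality of life leaves ten, which are the ten ESAS symptoms.

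**3. Error rate if any one significant item is read as benefit.** Under no effect, each two-sided 0.05 test has a 0.025 chance of falsely favouring music. With independent items:

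- favouring music: 1 − 0.975^10 = 0.224
- either direction: 1 − 0.95^10 = 0.401

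Symptoms are correlated, which lowers these figures. For ten normal test statistics with common correlation ρ and c = 1.960:

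P(at least one favours music) = 1 − ∫ φ(x) · Φ((c − √ρ·x)/√(1−ρ))^10 dx

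The two-sided version replaces Φ(·) by the probability of lying between −c and c.

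| Assumed ρ | Favouring music | Either direction |
|---|---|---|
| 0 | 22.4% | 40.1% |
| 0.2 | 19.5% | 37.7% |
| 0.3 | 17.8% | 35.1% |
| 0.4 | 16.1% | 32.1% |
| 0.5 | 14.4% | 28.7% |
| 0.6 | 12.5% | 25.1% |
| 0.8 | 8.6% | 17.3% |
| One test only | 2.5% | 5% |

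A simulation of 20,000 null trials per correlation, with 33 per arm, normal items and two-sample t-tests, agrees: 19.3%, 16.1% and 12.4% favouring music at ρ = 0.2, 0.4 and 0.6.

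**4. Power under the alternatives.** For a 2-point difference with SD 2.5 (standardised difference 0.8) and 33 per arm, t-based power is 0.893 at alpha 0.05 and 0.634 at alpha 0.005 (= 0.05/10). The normal approximation gives 0.901 and 0.671.

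**5. The overall score as defined.** The physical component has six items and the psychological component two, so the score covers eight of the ten symptoms. Sleep disorders and malaise are in neither component. The documents give no SD or relevant difference for this score, so its power cannot be computed.

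**The case against.** The strongest reply is that the protocol states no success rule. The 0.05 sentence is a reporting convention that also covers analgesic use and nurse visits, and reading any single item as success is the reader's addition. This stands in part: the percentages are conditional on that reading and must be given so. It does not remove the point, because nothing in the text names what would decide instead.

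Second, the regression is added to the before-after tests, which are not limited to single items, and its list is said to apply case by case. An analysis of the overall score is therefore not excluded. That is so, but those tests are paired, and no between-arm test of the overall score is written anywhere.

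Third, this is a condensed article, and endpoint ranking and multiplicity control are often left to an analysis plan. Silence alone would be no finding. Here, however, the text names the dependent variables and sets one threshold for all results. A later plan would have to change that text, not only add to it.

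A reader might infer a stronger claim: that the false-positive risk is about 16%, or one trial in six. The documents do not support that as a fact. It needs an inter-item correlation near 0.4, whereas the Background says only that symptoms are related. It also must be set against 2.5%, not against the two-sided 5%.

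**Conclusion.** The mismatch between defined, sized and modelled outcome is real and lies in the stated text. Its size can be given only as a conditional range. If one significant item were reported as symptom benefit, the false-claim probability would be several times nominal at any plausible correlation: about 12% to 19% for correlations of 0.6 to 0.2 against 2.5%, or about 25% to 38% in either direction against 5%. Even at 0.8 it is more than three times nominal (8.6/2.5 = 3.4).

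These figures assume a common correlation that the documents do not give, approximately normal test statistics, and unadjusted comparisons in place of the covariate-adjusted regressions on 0 to 10 items that are planned. They do not show that the investigators intend to claim success on any single item.

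**What to change.** In Statistical analysis, name one between-arm comparison at T1 as the only test that decides the patient efficacy claim, at two-sided 5%, and limit the decision role of the 0.05 sentence to it.

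- **Natural choice: anxiety.** It is the item the trial was sized on, so the planned power of about 90% carries over.
- **If the overall ESAS score is preferred,** first state which items it contains, and acknowledge that the documents give no SD or relevant difference from which to state its power.

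Report the remaining items as secondary with 95% confidence intervals. If single-item claims are to be made from them, adjust their p-values, for example by Holm.

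The cost is a few sentences and no new data. The downside is a stricter threshold for single-item claims: with 33 per arm, power for a 2-point effect with SD 2.5 falls from about 89% to about 63% at 0.005, the strictest Holm step for ten items. With nine remaining items that step is 0.05/9 = 0.0056, so the loss is slightly smaller. The deciding test itself loses nothing.
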